## Abstract

**Background:**

Adequate implementation of work-related stress management interventions can reduce or prevent work-related stress and sick leave in organizations. We developed a multifaceted integral stress-prevention strategy for organizations from several sectors that includes a digital platform and collaborative learning network. The digital platform contains a stepwise protocol to implement work-related stress-management interventions. It includes stress screeners, interventions and intervention providers to facilitate access to and the selection of matching work-related stress-management interventions. The collaborative learning network, including stakeholders from various organizations, plans meetings focussing on an exchange of experiences and good practices among organizations for the implementation of stress prevention measures. This paper describes the design of an integral stress-prevention strategy, Stress Prevention@Work, and the protocol for the evaluation of: 1) the effects of the strategy on perceived stress and work-related outcomes, and 2) the barriers and facilitators for implementation of the strategy.

**Methods:**

The effectiveness of Stress Prevention@Work will be evaluated in a cluster controlled trial, in a large healthcare organization in the Netherlands, at six and 12 months. An independent researcher will match teams on working conditions and size and allocate the teams to the intervention or control group. Teams in the intervention group will be offered Stress Prevention@Work. For each intervention team, one employee is responsible for applying the strategy within his/her team using the digital platform and visiting the collaborative learning network. Using a waiting list design, the control group will be given access to the strategy after 12 months. The primary outcome is the employees’ perceived stress measured by the stress subscale of the Depression, Anxiety, and Stress Scale (DASS-21). Secondary outcome measures are job demands, job resources and the number of preventive stress measures implemented at the team level. Alongside the trial, a process evaluation, including barriers and facilitators of the implementation of Stress Prevention@Work, will be conducted in one healthcare organisation.

**Discussion:**

If Stress Prevention@Work is found to be effective in one healthcare organisation, further implementation on a broader scale might lead to increased productivity and decreased stress and sick leave in other organizations. Results are expected in 2018.

**Trial registration:**

NTR5527. Registered 7 Dec 2015.

## Background

In Europe, one in four employees experience work-related stress [1]. Work-related stress can adversely influence health and cause a substantial amount of sick leave in organizations. Common mental disorders related to work-related stress, such as depression and anxiety, contribute the most to this sick leave [2, 3]. For example, the percentage of total number of sick leave days caused by psychological complaints, being stressed out, or being burned out was 22% in the Netherlands in 2015 [4].

Organizational work-related stress management interventions have shown positive effects on both sick leave and productivity [5, 6]. In addition, organizational work-related stress management interventions have shown positive effects on employee outcomes, such as confidence, coping, general health, and job satisfaction [7–10]. In addition to organizational interventions, stress management interventions on an individual level (e.g., a mindfulness program or assertiveness training) have shown positives effects on employees’ mental health, such as perceived stress, emotional exhaustion and anxiety state [10, 11]. Given the body of evidence, it is surprising that work-related stress management interventions are rarely used by organizations [12], in particular since the costs related to the consequences of work-related stress are high.

The key issue appears to be an implementation problem. Given the large number of available stress prevention strategies available on search engines such as google, information overload is likely. This results in difficulty selecting an intervention that fits well within an organization. Previous studies have shown that barriers associated with the implementation of work-related stress management interventions in organizations are present on three levels: sector, organization and employee [13]. To overcome implementation barriers at various levels across organisations, a combination of strategies has proven to be more effective than a single strategy [14, 15]. Therefore, we have developed a multifaceted, integral stress prevention strategy, Stress Prevention@Work (SP@W), to facilitate the selection and use of interventions in organizations. SP@W consists of two elements: 1) a digital platform (DP), which is an information technology platform containing a stepwise protocol to select and implement work-related stress management interventions, and 2) a collaborative learning network. The DP facilitates access to and the selection of matching work-related stress management interventions (evidence-based and/or practice-based). Interventions can be tailored to the specific needs of the team or organization either by someone within the organization or by an external coach or an implementation specialist. In previous research, a stepwise protocol has been shown to be effective by providing a framework for organizations that can be used to make suitable choices for work-related stress management interventions [16–18]. In addition to the DP, we initiated a collaborative learning network that provides contact between organizations to allow and facilitate the exchange of lessons learnt during the implementation of work-related stress management interventions. The network builds on earlier research showing that for the selection of suitable interventions, organizations often rely on a limited network of peer organizations for information about interventions [15, 19].

This paper describes SP@W and the protocol for the evaluation of SP@W by a cluster controlled trial, including an intervention and control group. We hypothesize that SP@W will decrease the employees’ perceived stress by reducing implementation barriers and increasing the implementation of work-related stress management interventions. A process evaluation will be guided by the framework of the Nielsen & Randall model for process evaluation of organizational interventions [20], while taking into account criteria described by Steckler and Linnan [21] that are relevant to the implementation process of SP@W, including barriers and facilitators.

## Methods

First, we describe SP@W, and next the protocol for the effect and process evaluation of SP@W.

### Integral stress prevention strategy Stress Prevention@Work (SP@W)

SP@W consists of two elements: 1) a digital platform (DP) with a stepwise protocol to select and implement work-related stress management interventions, and 2) a collaborative learning network. This two-element strategy was developed in close collaboration with several organizations from various sectors, including the healthcare sector. This participatory format enabled tailoring of the strategy to the needs of organizations. This is necessary because work-related stress has a wide range of determinants [8, 22]. Both elements of SP@W are described below.

### Digital platform (DP)

The DP consists of a stepwise protocol, multiple interventions, and screening instruments. The stepwise protocol consists of with five steps: 1) awareness, 2) assessment, 3) prioritizing and planning, 4) implementation, and 5) evaluation. The interventions are either at organizational or employee level with a focus on: online or offline groups or individuals; primary or secondary prevention, or specific sectors and organization types (e.g. small vs. medium-sized enterprises). An example of an offline organizational intervention is a guideline to start a dialogue between employees and their manager(s) about the presence of work-related stress within the organization or team [23]. An example of an individual online intervention is a self-help module to reduce work-related psychosocial risk factors [24]. Additionally, the DP provides screening instruments for (work-related) stress and psychosocial risk factors, and contains references to intervention providers who can assist in the implementation process if needed.

#### Development of the digital platform

We piloted the DP in five organizations in the educational, healthcare, transport and ICT sector aiming to achieve the optimization of the DP for use in multiple sectors. Supervisors, managers and Human Resource (HR) managers participated in these sessions. At the end of each session, a structured interview was performed about several aspects of the usability of the DP within their organisation, such as feasibility and accessibility, attitude towards the DP, motivation for use, financial feasibility, barriers, facilitators, and satisfaction. Based on these sessions, we optimized the DP to ensure that the steps of the DP’s stepwise protocol were easy to follow for the target group of HR managers in medium or large organizations.

#### The stepwise protocol

The first step focuses on evaluating the awareness and commitment the organisation. The second step focuses on finding or confirming the main work-related psychosocial risk factors of stress within a team and prioritizing the risks that will be tackled. The third step focuses on choosing the appropriate intervention(s). The fourth step focuses on implementing the chosen work-related stress management intervention(s), and the fifth step focuses on the evaluation of the process and effects, and evaluates if further interventions are necessary. The steps are described below.

##### Step 1 Awareness of stress in the workplace

Step 1 focuses on evaluating the awareness and level of stress present at the workplace, within a team, or in the organization using a multiple-choice question “*Is there stress at your workplace or in your organization?”* The answer categories are: “*Yes, there is stress at the workplace, we have an accurate idea of the problems”, “Yes, there is stress at the workplace, however we have no accurate idea of the problems”, “We do not know if there is stress at our workplace”,* and “*No, there is no stress at our workplace, but we want to focus on prevention of stress.”* The DP contains corresponding background information for this step focusing on indications of work-related stress and statistics of work-related stress across various sectors in the Netherlands.

##### Step 2 Problem assessment

Step 2 has a checklist with work-related psychosocial risk factors, presented in themes (Table 1). A priority level is chosen for each risk factor: “high priority”, “low priority”, “unknown”, or “no problem”*.* The checklist is based on literature about psychosocial risks and work-related stress. A preliminary list was discussed during a project meeting with all researchers involved in the development of the SP@W until consensus about the checklist was reached.

**Table 1 Tab1:** Work-related psychosocial risk factors of stress, consequences and personal characteristics discussed on the digital platform

Themes	Examples
Psychosocial risk factors at work	
Job demands	Quantitative job demands, emotional requirements and cognitive load at work
Decision latitude and control	Task variety and autonomy
Social support	Supervisor and co-worker support
Violence and harassment	Violence, harassment and bullying—internal by colleagues or management or third party by clients, patients or the public
Job security	Precarious work, restructuring, temporary employment contracts
Consequences	
Work-life balance	Work-home interference and home-work interference
Health and resilience	Burnout or stress complaints and general health
Satisfaction	Job satisfaction
Performance and absence	Absenteeism, presenteeism, personnel turnover and productivity
Personal characteristics	
Personal resources	Coping style (active/passive)
Qualification	Education level, skills level

The DP provides background information on how to prioritize the work-related psychosocial risk factors and how to involve management or other team members in the identification and prioritization of psychosocial risk factors at work. It also provides suggestions on how to use information gathered earlier about work-related stress in the organization (e.g., an employee satisfaction survey). A questionnaire can be distributed within the team to measure work-related stress more accurately, if needed.

##### Step 3 Deciding on interventions

Based on the priorities identified in step 2, one or more work-related psychosocial risk factors are selected in step 3. The intervention teams then decide on the number and type of intervention(s) for implementation. A search engine connects the selected work-related psychosocial risk factors to matching stress management interventions. The search engine contains a short description of each intervention, including information about the type of intervention (e.g. individual or team programs) and the costs (“free of charge” or “costs involved”). In addition to the interventions provided by the search engine, interventions already available in the participating organization or a tailored intervention offered by a consultant are also available for selection. Apart from choosing an intervention or a consultant to provide a tailored-made intervention, good practice examples are available on how other organisations tackled psychosocial risks. Background information in this step focuses on how to make an action plan for the implementation of the stress management intervention and how to involve the employees.

##### Step 4 Implementation

In step 4, an action plan to implement the work-related stress management intervention(s) (selected in step 3) is made and the intervention is implemented. This plan includes who does what at which time in order to implement the intervention as planned. This step offers background information on how to foster good communication about the implementation of an intervention with the employees and/or management, and how to keep track of the implementation process, for example, by asking the employees how they experience the implementation of the intervention.

##### Step 5 Evaluation

Step 5 focuses on the evaluation of the process and effect of the implemented stress-management intervention using questionnaires. This information informs the organisation about what went well, and which parts should be adjusted in the future. The process evaluation questionnaire includes questions about three topics: 1) satisfaction with the results and process (e.g. “How satisfied are you [up to now] with the implementation process of the intervention?”), 2) factors for success and improvement, such as experienced support (e.g. “How satisfied are you with the support from the organisation during the implementation process?”), and 3) an open-ended question about changes during the implementation period (“Did the action plans (step 4) change during the execution of this project?”). The first two questions are answered using a 10-point Likert Scale. A report is automatically generated and includes an overview of the results. The effect evaluation is a checklist that is similar to the work-related psychosocial risk factors checklist in step 2 *‘Assessment of the problems’*. By completing this checklist, the stepwise protocol can be continued with a new round. Background information available in step 5 involves advice about evaluation methods.

### Collaborative learning network

The second element of SP@W is the collaborative learning network. The collaborative learning network aims to stimulate communication between organizations in enabling, sharing, and exchanging knowledge about implementation experiences and discussing good practices about implementing a stress-management intervention, and case histories for implementation between organizations. The aim of this network is that organization may learn from the other organizations, but may also be stimulated and energized by other organizations. Three learning networks were set up in three regions in the Netherland, including stakeholders from 20 distinct organizations from several sectors. We aim to organize three learning-network meetings over the trial one-year trial period, across all three regions, and one annual general meeting for all geographic regions together. Each meeting is approximately two hours, and addresses, e.g., one specific step from the stepwise protocol guided by the specific needs of the participating organizations. The meetings are chaired by an implementation expert.

### Effect and process evaluation of Stress Prevention@Work

#### Study design and measurements

The effectiveness of SP@W will be evaluated in a cluster controlled trial. The study population consists of employees of a Dutch healthcare organization. This organization has more than 4000 employees throughout the Netherlands, who are organized in self-directing teams. The organization facilitates care in nursing homes (including geriatric rehabilitation care), residential care homes, and home-based care. SP@W will be implemented in intervention teams during the first six months of the trial period. After the final follow-up measurement (12 months after baseline), SP@W will also be offered to the control teams. Digital questionnaires will be sent to employees from both the intervention and control teams at baseline and after six and 12 months to measure the short- and long-term effectiveness of SP@W. To maximize the response rate, two reminders will be sent to the employees for each questionnaire. The questionnaires will be in Dutch. The SP@W implementation process will be assessed by performing a process evaluation. The study procedures and design have been approved by the Medical Ethics Committee of the VU University Medical Center, Amsterdam, The Netherlands (2015.480).

### Recruitment, and inclusion and exclusion criteria

Recruitment of employees from a healthcare organization will involve a stepwise procedure. First, the management will decide which unit of the organisation will participate in the trial. Next, team coaches from the participating unit will be asked to select eligible teams to participate in the trial. Eligibility implies that the teams are willing to participate in the trial and able to provide a team member who will be responsible for the implementation of SP@W within the team during the trial period. A Human Resource (HR) manager or the team coach can also choose to take responsibility for implementing the SP@W within a team. Second, the employees within the eligible teams will receive an e-mail with the study information, inclusion and exclusion criteria, and the baseline questionnaire. The inclusion criteria are a minimum age of 18 years and an employment contract at the healthcare organization. Exclusion criteria are sick leave of more than one month at the time of inclusion or planned retirement within one year. Informed consent for participation in this study will be retrieved through an opt-in construction in accordance with the Dutch law on Medical Research in Humans. By completing the baseline questionnaire, eligible workers declare their agreement to participate in scientific research.

### Allocation and matching teams

After the baseline measurement, teams will be matched on their specific work setting (e.g. home-based care or nursing home care) and team size. The aim is to have both comparable teams and an equal number of participants in the intervention and control condition. This information will be obtained from the team coaches. Following the match, allocation to the two conditions will be performed by an independent researcher who does not have information about the perceived stress levels in the teams. After allocation, the teams are informed about the condition they are assigned to: intervention or control (waiting list) condition. A secure login code for the digital platform (DP) for all intervention teams will be sent to the employees responsible for applying SP@W within their team. The use of the DP will be explained during a training by an implementation expert. An invitation for this training will be sent to all responsible employees for the intervention teams. They will also receive an invitation for collaborative learning network meetings and the contact information of all employees responsible for the DP in the intervention teams.

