### Strengths and limitations

The first strength of this study is our controlled design. This allows for a comparison between teams within the participating healthcare organization who are exposed to similar environmental conditions that may lead to stress (e.g. organizational changes), if not for access to SP@W. The second strength of this study design is the follow-up period of one year, which allows insight into short-term effects of the intervention after six months and in the longer term after 12 months. Third, by incorporating a process evaluation, we will gain insight into the strategy’s implementation process within the intervention teams. Last, this study will be executed in a real-life setting, which will make it easier to generalize the effects to similar healthcare organizations.

Since SP@W focuses on the organization and not on individual workers, individual randomisation is not feasible. Matching controls may induce bias since matching a limited number of known parameters may lead to differences between teams in the intervention and control group that we are unaware of. Furthermore, we cannot completely rule out contamination since all teams belong to one healthcare organization. A cross-over of information can reduce the contrast between the groups and consequently, the impact of the effects.

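### No random step is stated for allocating the matched teams and no reason is given against one, so the plan accepts avoidable confounding by unmeasured team factors

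*Protocol article*

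**What the plan says.** All references are to the protocol article.

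- **Design label.** Study design and measurements: "The effectiveness of SP@W will be evaluated in a cluster controlled trial". The abstract and the Background use the same label. The design is nowhere called randomised.
- **Selection of teams.** Under Recruitment, and inclusion and exclusion criteria, "team coaches from the participating unit will be asked to select eligible teams to participate in the trial". Eligible teams must be willing and able to supply someone responsible for implementation.
- **Matching.** Allocation and matching teams: "After the baseline measurement, teams will be matched on their specific work setting", and also on team size. The aim is comparable teams and "an equal number of participants in the intervention and control condition". On the source of the matching data: "This information will be obtained from the team coaches".
- **Allocation.** Same section: "allocation to the two conditions will be performed by an independent researcher who does not have information about the perceived stress levels". Teams are told their condition afterwards.
- **Rationale and limitation.** Strengths and limitations: "Since SP@W focuses on the organization and not on individual workers, individual randomisation is not feasible". It then concedes: "Matching controls may induce bias since matching a limited number of known parameters may lead to differences between teams" of which the authors would be unaware.

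**The concern.** The allocation section says who assigns the teams and what that person does not know. It does not say by what mechanism a team goes to one arm or the other. Together with the consistent controlled label and a limitation paragraph that relies on matching for comparability, the natural reading is that no chance mechanism is used.

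The only feasibility statement concerns individuals. It explains why the unit of allocation is the team, but leaves open why teams are not randomised. That matters because the limitation the authors concede, unknown differences left after matching on a few known factors, is what a random draw among the matched teams is meant to deal with.

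The comparison of perceived stress between arms is at stake. Matching controls two team characteristics. Keeping the allocator unaware of stress levels guards against selection on the baseline outcome. Neither protects against systematic differences on other prognostic features of a team. The planned multilevel analysis accounts for correlation within teams but does not remove such differences.

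**Working it through.** **Step 1. Which elements of a cluster-randomised design are already present?**

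| Element needed | Where the article provides it |
|---|---|
| Teams identified and willing before allocation | Recruitment, and inclusion and exclusion criteria |
| Baseline measured before allocation | Allocation and matching teams |
| Matched sets (work setting, team size) | Allocation and matching teams |
| Allocation by an independent person | Allocation and matching teams |
| Teams informed only after allocation | Allocation and matching teams |
| Control teams get the strategy after 12 months | Study design and measurements |
| Chance mechanism within matched sets | Not stated |
| Reason for not randomising teams | Not stated; the reason given concerns individuals |

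Only the draw is missing, and nothing in the article stands against it.

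**Step 2. Would randomising teams change the sample size?** The stated figure reproduces. Inputs from Sample size: SD 3.81, target difference 1.5, power 0.80, alpha 0.05. Statistical analyses gives a two-tailed test.

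- n per group = 2 × (1.960 + 0.842)² × (3.81/1.5)² = 101.3, rounded up to 102, or 204 in total. The t-based version gives 102.2, rounded up to 103, or 206 in total. The plan states 104 per group, 208 in total.
- Dropout: 208/0.75 = 277.3, rounded up to 278, as stated.

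None of these inputs depends on how teams are assigned, so a random draw leaves the calculation as it is.

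**Step 3. How much could an imbalance matter?** The article gives no figure for residual imbalance, so this step is an illustration over an assumed range. Let b be the systematic difference between arms in follow-up stress when there is no true effect.

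- SE of the arm difference = 3.81 × √(2/104) = 0.528, ignoring clustering.
- Chance of a significant result in either direction = Φ(b/SE − 1.96) + Φ(−b/SE − 1.96).

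The last column repeats this with a design effect of 1.55, which is also an assumption: the article gives no intraclass correlation and no team size. SE = 3.81 × √(2 × 1.55/104) = 0.658.

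| b (assumed) | Share of 1.5-point target | Rejection rate, no clustering | Rejection rate, design effect 1.55 (assumed) |
|---|---|---|---|
| 0.25 | 17% | 8% | 7% |
| 0.50 | 33% | 16% | 12% |
| 0.75 | 50% | 29% | 21% |
| 1.00 | 67% | 47% | 33% |

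The nominal rate is 5%. The table compares unadjusted follow-up means and does not show what would remain after baseline adjustment. An imbalance in the other direction could hide a real effect.

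**The case against.** **The text never says that allocation is not random.** That is correct. The article is a condensed account and is silent on the mechanism. The reading rests on the label, the silence and the limitation paragraph together. If a draw was intended, the allocation section still needs a sentence saying so, and the label should change. The passage needs correcting on either reading.

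**A reader might infer that the allocator acts on coach preference, readiness or workload.** The document does not support this. The information taken from the coaches is mentioned directly after the matching factors, and nothing says that anything else reaches the allocator, who is described as independent. Coaches do select the teams, but before allocation and for both arms, and willingness is required of every team. The procedure as described does not rule such influence out, but it gives no evidence of it.

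**The statement about individual randomisation is not offered as the reason for not randomising teams.** This is a fair point. It is more accurate to say that no reason is given than that a stated reason fails.

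**The limitation is disclosed, and a matched controlled trial is a recognised design.** Both are true, and nothing is concealed or contradicted. Disclosure does not answer the point that this limitation could have been avoided within the procedure described.

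**A reader might conclude that no effect could be attributed to the strategy, or that the p-value would be meaningless.** That goes too far. There is a pre-allocation baseline, recorded prognostic factors, concurrent controls from the same organisation and a multilevel analysis. Model-based inference remains possible, but it depends on the untestable assumption that unmeasured team factors do not confound the comparison.

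**The illustration is not evidence.** That is also correct: the assumed imbalance, not the protocol, produces the rejection rates.

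**Conclusion.** The point holds in this form: no random step is stated for the matched teams, no reason is given against one, and every other step needed for it is described. The plan therefore accepts confounding by unmeasured team factors that it could avoid. Non-random allocation is an inference from the text, although the natural one.

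The size of any bias cannot be derived from the document. Under assumed imbalances of 0.25 to 1.0 points, the false-positive rate would run from about 8% to 47% without clustering, or about 7% to 33% under the assumed design effect. These figures show how sensitive the comparison is and do not predict what will happen. A random draw would not guarantee balance in a given trial. It would remove systematic allocation bias and leave chance differences, which the analysis is built to handle.

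The point bears on the primary comparison and cannot be repaired by design once teams have been allocated.

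**What to change.** **If teams have not yet been allocated.** In Allocation and matching teams, state that within each matched pair or set (work setting, team size) the independent researcher assigns teams by a concealed, computer-generated random sequence after baseline closes. Then change the design label to cluster-randomised wherever it appears, and revise the paragraph in Strengths and limitations that presents matching as the safeguard.

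**If allocation has already been made non-randomly.** Keep the controlled label. Say why teams were not randomised, prespecify adjustment of the primary analysis for baseline DASS-21 stress and the matching factors, and limit the causal conclusion accordingly. The article is written in the future tense but gives a December 2015 registration and expects results in 2018, so this case needs an answer.

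**Cost.** An amendment and a registry update. On the plan's own description, sample size, recruitment and data collection stay as they are.
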